### Hypothesis

There are 4 main hypotheses this study will test. First, subjects randomized to adaptive interventions that begin with nurse-led groups will show greater increases in diabetes self-management behaviors than those who begin with *promotore*-led groups. Second, among nonresponders to either of the first-line approaches, subjects randomized to a multifamily, problem-solving group will show greater improvements than those assigned to a single-family approach. Third, key relative’s participation in treatments will lead to (1) increased patients’ and relatives’ diabetes knowledge; (2) increased diabetes self-efficacy; (3) increased collaborative goal setting by families with health care providers; (4) increased family support; and (5) increased T2DM self-management behaviors. Fourth, subjects who are older, female, less educated, and less acculturated have an alcohol use or psychiatric disorder or have a longer history and greater severity of T2DM will (1) be less likely to have family members participate in treatment and (2) use diabetes self-management skills less often.

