### Initial Intervention: Tomando Control

The initial intervention, called “Taking Control of your Diabetes” or in Spanish “*Tomando Control de su diabetes*,” consisted of 6 biweekly sessions lasting 2.5 hours each led either by 2 trained *promotores* (*promotore*-led group) or by RNs (RN-led group). Each session included 10-12 patients. Patients’ families or friends were encouraged to attend sessions, which were held at Olive View-UCLA Medical Center. Each participant received a copy of the companion book, an audio relaxation tape, and an audio exercise tape with a booklet to supplement the material covered during the workshop sessions. The following topics were covered in sessions: (1) techniques to deal with the symptoms of diabetes and associated condition, (2) appropriate exercise, (3) healthy eating, (4) correct use of diabetes medications, and (5) working more effectively with health care providers in a collaborative partnership. Patients were expected to make weekly action plans, share experiences, and help each other solve problems they encountered in creating and carrying out their self-management strategies. The classes were highly participative and allowed participants to show mutual support and develop confidence in their abilities to manage their health. The program is based on the Stanford School of Medicine’s Chronic Disease Management Program developed by Lorig et al [36] and culturally adapted by Mauldon et al [37]. Similar program content was delivered in each group, with the only difference being the type of trainer: *promotore* versus RN.

Early response status was determined after the third TC session (ie, 6 weeks after starting the intervention). An independent evaluator blind to study condition used the Summary of Diabetes Self-Care Activities (SDSCA) to assess diabetes self-management behavior. A subject was considered an early responder if he/she showed a gain of 50% over baseline on the SDSCA. Early responders continued to receive the TC intervention that they were originally assigned. Nonresponders, those subjects who did not show a gain of 50% over baseline, were rerandomized to receive either the stepped-up, family-focused TC approach or the MFG. The following sections describe these 2 interventions.

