### Second Intervention: Family-Focused TC Approach

For those subjects who were randomly assigned to receive the augmented TC, the TC clinician (either a *promotore* or nurse, depending on the original group assignment) conducted up to 3 home visits that were designed to explain the purpose of the TC intervention to a key relative so as to reengage the family member in the group process. Each visit was carefully scripted to address the family’s role in helping the family member with diabetes. The first home visit was focused on the family’s reaction to having a loved one with diabetes and was designed to elicit how the family functioning had changed since the diagnosis was made. The second session aimed to help the family set realistic goals for participation in TC including the length of the groups and the expectations of the family in using the material covered in the group to effect behavior change. Logistical details (eg, which family member would accompany the patient to the group, how they would get to the group, and so on) were identified and obstacles to attendance were resolved. The third session solidified the gains made in the first 2 sessions as well as emphasized to the family that the *promotore* or nurse was available for crises or problem resolution if last-minute difficulties arose prior to the TC group. These engagement strategies have been very effective in increasing the participation of family members in group therapy [38].

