### Data Collection and Measures

Table 2 lists the measures to be used at each assessment point. Assessments were done at baseline and at 3, 6, and 12 months. In addition, the primary outcome variable (ie, diabetes self-management behaviors) was measured 6 weeks after the start of the first phase of the study to determine progress over time and the need for a change in treatment strategy. All measures were collected by a research assistant blind to the experimental conditions. Characteristics of the sample were measured at the initial visit including various demographic and clinical information.

The primary outcome is the difference in response scores of the SDSCA between the 4 groups at 3, 6, and 12 months after baseline [40]. The SDSCA is a well-validated instrument with excellent psychometric properties in several languages including Spanish [41,42]. It is the instrument most frequently used for assessing the acquisition of diabetes self-management behaviors [43]. The SDSCA is formatted to ask on how many of the previous 7 days the individual performed recommended self-management activities: eating healthy foods, following a diabetic diet, exercising, self-monitoring of glucose, and caring for one’s feet. A weekly self-care score ranging from 0 to 7 is generated, with higher scores corresponding to greater number of days carrying out the recommended behaviors.

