### Statistical Analysis

Data analysis will be conducted by intent-to-treat with participants analyzed according to their randomized intervention regardless of attendance. Our primary analytical tool will be the generalized linear mixed model (GLMM) [52,53]. GLMMs accommodate multiple outcome types in a unified framework via an appropriate link function (identity link for continuous normally distributed measures; logistic link for binary measures); allow for both fixed and time-varying covariates; automatically handle missing data, producing unbiased parameter estimates provided observations are missing at random; and appropriately account for the correlations induced by repeated measurements within subjects. We will fit GLMMs with fixed effects for the intercept, time (baseline, 3, 6, and 12 months), group, and a group-by-time interaction term, where the definition of group depends on the hypothesis and an unstructured covariance matrix. Model diagnostics will be used to determine suitability of more parsimonious (eg, autoregressive) correlation structures and nonlinear (eg, quadratic) effects for time. A sample size of 330 patients will provide 90% power to detect a difference of 0.29 in the score of SDSCA between the study groups. Subgroup analysis will be performed to determine if some moderators differentially affect the outcome such as patients’ age, gender, educational levels, duration of diabetes, and baseline HbA1c levels.

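### As written, the model for the second hypothesis appears to omit the first-stage arm (nurse or promotore); adding it is nearly free and recovers a little precision

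*Protocol article*

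**What the plan says.** - **Model.** The Statistical Analysis section lists as fixed effects the intercept, time (baseline and the three follow-ups), "group, and a group-by-time interaction term, where the definition of group depends on the hypothesis". It gives one group factor per hypothesis and names no further covariate for the second hypothesis.
- **Contrast.** The Hypothesis section states the second hypothesis thus: "among nonresponders to either of the first-line approaches, subjects randomized to a multifamily, problem-solving group will show greater improvements". The comparator is the single-family approach, and nonresponders from both first-line arms are taken together.
- **Second randomization.** The section on the initial intervention says: "Nonresponders, those subjects who did not show a gain of 50% over baseline, were rerandomized to receive either the stepped-up" TC approach or the MFG. It states neither the allocation ratio nor whether allocation was stratified by first-stage arm.
- **Who delivers stage two.** In augmented TC the clinician is a promotore or a nurse, "depending on the original group assignment". The Joining Sessions section says the same of the MFG joining sessions, and the Ongoing MFG Sessions section has the same clinicians lead all later sessions.
- **Expected leader effect.** The first hypothesis predicts larger gains in self-management when treatment starts with nurse-led groups.

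**The concern.** The rerandomized patients form a two-by-two layout: leader type (nurse or promotore) by second-stage option (MFG or augmented TC). Both factors are randomized in the design, and leader type runs through both stages. A model whose only treatment factor is the second-stage option leaves any leader effect in the residual variance, although the trial's first hypothesis says there is one.

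Three things are at stake, all modest:

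- some precision for the second hypothesis, which has only the nonresponders to work with;
- a standard error that matches the allocation method, if rerandomization was stratified by arm;
- an answer to whether MFG performs differently after a nurse start and after a promotore start. The Objective in the abstract (which sequence works most efficiently, and for whom) calls for this, and a pooled two-level group cannot show it.

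**Working it through.** **Inputs from the article.** 330 patients, 165 per first-stage arm (Table 1); a detectable difference of 0.29 SDSCA points with 90% power (Statistical Analysis).

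**Assumptions.** The article gives no SD, alpha, sidedness or nonresponse rate. I assume two-sided 0.05, a single comparison of means, 1:1 rerandomization, and 40%, 60% or 80% nonresponse (132, 198 or 264 patients). The leader effect L among nonresponders is set at 0.29 and then varied from 0.10 to 0.80. The MFG effect is set at 0.29.

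**Step 1: the plan's figure.** The 90% cannot be reproduced without an SD; it can only be solved backwards:

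SD = 0.29 / [(1.960 + 1.2816) × √(2/165)] = 0.29 / (3.2416 × 0.1101) = 0.813.

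A one-sided 0.05 test would imply 0.900. I use 0.813.

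**Step 2: standard error with and without the arm term.** A factor split 50/50 with effect L adds L²/4 to the variance. At L = 0.29 that is 0.0210 against SD² = 0.660, or 3.1% of the total variance.

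SE ratio = √(1 + 0.25 L²/SD²) = √(1 + 0.0210/0.660) = 1.016.

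At 198 nonresponders (99 per option):

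- adjusted SE = 0.813 × √(2/99) = 0.1155;
- unadjusted SE = 0.1155 × 1.016 = 0.1173.

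**Step 3: power for an MFG effect of 0.29, with L = 0.29.**

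| Nonresponders | Without arm | With arm |
|---|---|---|
| 132 | 52.3% | 53.6% |
| 198 | 69.6% | 70.9% |
| 264 | 81.4% | 82.6% |

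**Step 4: other leader effects, 198 nonresponders.**

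| L | SE ratio | Power without arm | Power with arm |
|---|---|---|---|
| 0.10 | 1.002 | 70.8% | 70.9% |
| 0.29 | 1.016 | 69.6% | 70.9% |
| 0.50 | 1.046 | 67.0% | 70.9% |
| 0.80 | 1.115 | 61.5% | 70.9% |

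**Step 5: chance imbalance in leader type.** If rerandomization was not stratified, the difference in nurse share between the two options has SD √(4 × 0.25/198) = 0.071. Multiplied by L = 0.29, this shifts the MFG estimate with SD 0.0206 and a 95% limit of 0.040. The unadjusted standard error already contains it: √(0.1155² + 0.0206²) = 0.1173, the value in Step 2.

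**Step 6: simulation.** 10,000 runs, 200 nonresponders, no MFG effect, two-sided 5% test. The mean error of the MFG estimate was within 0.002 in every setting. Type I error was:

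| L | Rerandomization | Unadjusted | Adjusted |
|---|---|---|---|
| 0.29 | not stratified | 5.2% | 5.1% |
| 0.29 | stratified by arm | 4.8% | 5.1% |
| 0.80 | not stratified | 4.9% | 4.9% |
| 0.80 | stratified by arm | 2.8% | 5.0% |

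Under stratified 1:1 allocation the two estimates have the same spread (0.1154 at L = 0.29). The unadjusted analysis then merely overstates its standard error.

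**Step 7: what arm-specific estimates can show.** With about 99 nonresponders per arm (an even split of 198), the SE within an arm is 0.813 × √(2/49.5) = 0.163, so the 95% half-width is 0.32. The SE of the difference between arms is 0.163 × √2 = 0.231. These estimates are descriptive.

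**The case against.** The strongest reply is that the article never spells out group for the second hypothesis. It describes the primary outcome as follows: "The primary outcome is the difference in response scores of the SDSCA between the 4 groups at 3, 6, and 12 months after baseline". If those four undefined groups are the leader-by-option cells, the first-stage arm is already in the model. The section also notes that such models allow covariates, and a condensed article may leave covariates and stratification factors to a fuller document. This stands in part: one can say that the term appears to be missing, not that it is. A four-level group would still need a stated contrast for a hypothesis about patients "among nonresponders to either of the first-line approaches", and the article gives none.

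A second reply is that a pooled contrast answers the pooled hypothesis, and that the moderator list is only illustrative, so leader type is not excluded. This is correct, and it makes the arm-specific result a useful addition rather than a correction.

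A third reply is that 0.29 is a detectable difference between study groups, not a leader effect among nonresponders. Nonresponders are selected on their early gain, so the effect in them may differ. This also stands, and it is why a range of L is shown.

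A reader might go further and infer that leader imbalance biases the MFG effect, or that rerandomization was carried out within each arm. The article supports neither. Chance imbalance is ordinary sampling error that the unadjusted standard error covers (Steps 5 and 6). The article is also silent on stratification, and such silence is not an error in a condensed report.

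**Conclusion.** This is a minor improvement, not a validity problem. On the natural reading of the model and the second hypothesis together, the first-stage arm is left out although it is a randomized factor that persists into stage two and is expected to matter. The MFG test remains valid without it. With a leader effect of 0.29, SD 0.81 and about 200 nonresponders, the loss is about 1.6% in standard error and 1.3 power points. With stratified rerandomization the loss takes the form of a slightly conservative test (4.8% instead of 5%). The loss becomes material only for leader effects well above 0.29, and nothing in the article points to effects of that size. SD, alpha, sidedness, allocation ratio and nonresponse rate are all assumed here.

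**What to change.** For the second hypothesis:

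1. Define group as MFG versus augmented TC among nonresponders.
2. Add first-stage arm (nurse or promotore) and arm-by-time as fixed effects. Keep group and group-by-time as the tested terms. Treat the arm coefficient as an adjustment only: among nonresponders, who are selected after the first randomization, it does not estimate the effect of leader type.
3. State whether rerandomization was stratified by first-stage arm.
4. Report the MFG effect within each leader arm, with its interval, as a secondary and descriptive result.

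The cost is four degrees of freedom if time is a four-level factor (one for arm, three for arm-by-time). The variable is already recorded, so no new data are needed.

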### Ethics Approval

All participants signed an informed consent form. The trial protocol was reviewed and approved by the Institutional Review Board of the David Geffen School of Medicine at UCLA (#16-000434) and the Education and Research Institute of Olive View-UCLA Medical Center (#882988). Initial approvals were received in November 2016, and yearly renewal approvals were received throughout the course of the study. The 1-year follow-up assessments were completed in late 2021.

## Results

This study was funded by the National Institute of Nursing Research in June 2016 for a period of 5 years. Institutional review board approval was obtained in November 2016. Between March 2017 and September 2020, a total of 330 patients were recruited from the outpatient primary care clinics of Olive View-UCLA Medical Center, with a brief hiatus between May 2020 and July 2020 due to COVID-19 restrictions. The study interventions were completed in December 2020. Data collection began in March 2017 and was completed in December 2021. Data analysis is expected to be completed in Spring 2023, and results will be published in Fall 2023.

## Discussion

### Principal Findings

This paper describes the protocol of a sequential multiple assignment randomized trial to better understand how various factors in the design and implementation of a DSME program can affect the outcomes of participants with T2DM.

The first question we address is whether RNs are more effective than *promotores* in leading DSME programs for Latinx patients with T2DM. This study represents a direct test of the hypothesis that Latinx subjects assigned to RN-led groups will perform more diabetes self-management behaviors than subjects assigned to *promotore*-led groups. The findings of this aspect of the study could have important economic implications, particularly if subjects in RN-led groups do not achieve better outcomes than subjects in *promotore*-led groups because of the greater cost and lower availability of RNs than those of *promotores*.

The design of this study will also further our understanding of the efficacy of interventions that use MFGs and how these are compared with interventions that focus on individual families. The reasons that patients may fail initial DSME interventions are numerous and varied, such that it may be difficult for any individual educator—professionally trained or otherwise—to be able to address all barriers that arise for a patient. The incorporation of multiple families with similar backgrounds in the same community provides the opportunity for participants to offer their combined, cumulative perspectives and experiences in order to problem solve and support their peers. This is important not only because of the increased likelihood of identifying reasonable solutions but also because it could help build a stronger sense of self-efficacy and agency among participants while also decreasing stigma, shame, and isolation. Furthermore, because sessions are intended to address behaviors and beliefs among the entire family, we hope to gain additional insight into how these dynamics influence outcomes for participants in this program.

This study will also measure various demographic variables including age, gender, marital status, working status, educational level, acculturation level, comorbid medical and psychiatric disorders, and severity of diabetes. These will also be analyzed to explore whether particular characteristics of the sample can serve as potential predictors of outcomes.

### Comparison to Prior Work

There have been some studies that compared outcomes of patients with T2DM when counseled by RNs versus community health workers (the equivalent of *promotores*). The randomized trial by Babamoto et al directly compared the effectiveness of community health workers with case management and standard provider care in Latinx patients with T2DM for 6 months. In that study, patients in the community health worker group performed better than the other groups in several outcomes, namely higher retention rates, greater reduction in HbA1c concentrations, and medication adherence [16]. Kim et al compared outcomes in Korean Americans with T2DM, finding that patients counseled by community health workers had greater decreases in HbA1c concentrations than RN-counseled patients [54].

Several other studies using different methodological approaches have shown that interventions led by community health workers were cost effective and result in substantial reductions in diabetes complications. Ryabov et al estimated that interventions led by community health workers could result in an absolute reduction in projected probability of lifetime occurrence of nephropathy by 5.9%, neuropathy by 3.4%, retinopathy by 2.6%, and coronary artery disease by 3.8% [55]. Moreover, Brown et al suggested that *promotores* were most cost-effective among Latinx patients aged 50-65 years [56]. The benefits of community health workers extend to other ethnicities. For example, Huang et al found that home visits conducted by community health workers were highly cost-effective in a randomized study of 268 patients with T2DM in American Samoa [57]. We expect that our study will be particularly useful in building on this knowledge because the educational programming is standardized between both groups, with all participants receiving the same evidence-based intervention.

### Strengths and Limitations

Strengths of this study include its randomized design and inclusion of enough patients to allow for adequate statistical power and subgroup analysis. This study uses the SDSCA, which is a well-validated instrument to assess diabetes self-management behavior. It is the most widely used self-report instrument for measuring diabetes self-management in US adults [41]. In an appraisal of 26 psychometric tools of diabetes education, Eigenmann et al identified the SDSCA as 1 of 3 tools that met all expected criteria for validity, reliability, relevance, feasibility and acceptability, and responsiveness to change [58].

One potential limitation of this study is that the investigators were aware of the patients’ group assignment, and therefore bias in favor of any particular group cannot be excluded. However, every effort was made to ensure blinding. For instance, *promotores* and RNs were not aware of the purpose of the trial. An independent evaluator blind to study conditions was responsible for administering all study measures. A second limitation is the short duration of the trial (ie, 6 sessions over 3 months). However, many years of clinical experience and research data suggest that 6 intervention sessions are sufficient to result in clinically significant changes in diabetes self-management behavior [59].

### Conclusions and Future Directions

The findings of this trial should contribute to our understanding of the roles of community health workers, RNs, and family members in this area and may have important economic implications. Future research will focus on understanding the factors that affect self-management for Latinx patients with T2DM and will provide valuable information toward constructing an adaptive intervention that will help to determine which treatment strategies work to improve diabetes self-management behaviors most efficiently and for whom. Given the ever-increasing prevalence of T2DM, achieving better control of diabetes and lowering the associated medical complications experienced disproportionally by Latinx patients is a public health priority for a group that has long been underserved by current research and practice.

